### 3.2.2 Secondary Endpoints

The secondary endpoints are as follows:

- Time to resolution of overall 13 COVID-19 related symptoms which is defined as from Day 1 until the day at which the overall composite score of 13 COVID-19 related symptoms becomes 0 or 1 and remains at 0 or 1 for the rest of the Intake Period and for the Follow-up Period. Overall composite score of 13 COVID-19 related symptoms is the sum of 13 COVID-19 related symptom scores (i.e., cough, chills/repeated shaking with chills, muscle pain, fever, headache, anosmia/ageusia, shortness of breath, sore throat, gastrointestinal disturbance/symptoms, diarrhea, fatigue, nasal congestion, and chest tightness (CDC 2020). Each COVID-19 symptom will be recorded by patients on a scale of 0: Absent, 1: Mild, 2: Moderately severe, 3: Very severe. The overall composite score ranges from 0 (no symptoms) to 39 (very severe)
- Time to resolution of overall 8 cardinal COVID-19 related symptoms which is defined as from Day 1 until the day at which the overall composite score of 8 cardinal COVID-19 related symptoms becomes 0 or 1 and remains at 0 or 1 for the rest of the Intake Period and for the Follow-up Period. Overall composite score of 8 cardinal COVID-19 related symptoms is the sum of 8 cardinal COVID-19 related symptom scores (i.e., cough, chills/repeated shaking with chills, muscle pain, fever, headache, anosmia/ageusia, shortness of breath, and sore throat)
- Proportion of patients with reduction from Baseline (symptom present at Baseline) in each of 13 individual COVID-19 related symptom at EOI and Follow-up
- Proportion of patients with symptom becomes absent (symptom present at Baseline) at EOI and Follow-up for each of 13 individual COVID-19 related symptom
- Change from Baseline to EOI in overall composite score of 13 COVID-19 related symptoms
- Change from Baseline to EOI in overall composite score of 8 cardinal COVID-19 related symptoms
- Time to resolution of fever (defined as from Day 1 until the day at which a patient's daily maximum temperature achieves and remains below 100.4 °F for the rest of the Intake Period and for the Follow-up Period without an antipyretic medication)
- Proportion of patients with oxygen saturation <95% on Day 14 and Day 35

- Proportion of patients with oxygen saturation <98% on Day 14 and Day 35
- Measures collected from the Healthcare Provider Wellness Visits

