##### **4.3.4.1 Patient-assessed COVID-19 Symptom Score**

Symptom severity will be assessed based on how the patient is feeling at the moment. This will be recorded in TrialPace™.

Patients will self-assess the following 8 cardinal symptoms known to be associated with COVID-19 ([CDC 2020](#)):

1. Fever
2. Chills/Repeated shaking with chills
3. Cough
4. Shortness of breath
5. Headache
6. Muscle pain
7. Anosmia/ageusia
8. Sore throat

Additionally, patients will also report on the following 5 symptoms:

1. Gastrointestinal disturbance/symptoms (other than diarrhea as this will be assessed separately)
2. Diarrhea
3. Fatigue
4. Nasal congestion
5. Chest tightness

Patients will be instructed to rate their symptoms on a scale of 0-3 where:

- 0: Absent (no symptoms evident)
- 1: Mild (symptom present but easily tolerated)
- 2: Moderately severe (definite awareness of symptoms; bothersome but tolerable)
- 3: Very severe (hard to tolerate; interferes considerably with daily activity)

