**Table 3. Dose Up-titration of the Study Product**

| SP Administration Period | Dose (KB109)        |
|--------------------------|---------------------|
| Days 1–2                 | 9 g BID (18 g/day)  |
| Days 3–4                 | 18 g BID (36 g/day) |
| Days 5–14                | 36 g BID (72 g/day) |

Abbreviations: BID: Twice daily; SP: Study Product.

Doses should be taken at the same time each day. The morning dose should be taken by noon each day, and the evening dose should be taken approximately 8 hours after the morning dose. A missed morning dose may still be taken before noon on the same day; a missed evening dose may be taken within 4 hours of the routine daily evening administration dose.

Details of the patient's SP dosing (including the date, approximate time, and amount) will be recorded in SP dosing logs.

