### 7.3.1 Expectedness

An AE will be considered unexpected if the nature, severity, or frequency of the event is not consistent with the risk information described for the study product discussed within this protocol. The study product is characterized as a prebiotic non-digestible carbohydrate, which has the potential to be poorly tolerated due to local GI when taken at higher amounts. Undesirable GI effects can include acid reflux and heartburn, burping, flatulence, colic (spasmodic abdominal pain), borborygmi (flatulence in the bowels), laxation, reduced appetite, abdominal distension or pain, nausea, abdominal rumbling or an increased defecation frequency. At still higher amounts, watery stools and diarrhea can be expected.

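### The 13-symptom composite scores GI disturbance and diarrhea, both expected effects of KB109, so these two items push time to resolution and change to EOI against KB109

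*Protocol*

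**What the plan says.** Section 3.2.2 defines two composites, one of 8 cardinal symptoms and one of 13. The larger adds "gastrointestinal disturbance/symptoms, diarrhea, fatigue, nasal congestion, and chest tightness". Section 4.3.4.1 makes GI disturbance and diarrhea two separate items, each rated 0 to 3. For either composite, resolution is the day from which the sum "becomes 0 or 1 and remains at 0 or 1 for the rest of the Intake Period and for the Follow-up Period".

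Section 7.3.1 says the product "has the potential to be poorly tolerated due to local GI when taken at higher amounts", names a range of GI effects, and adds: "At still higher amounts, watery stools and diarrhea can be expected". Section 2.3 describes the adverse effects of this class of carbohydrates as dependent on dose, rapidly reversible and confined to the GI tract.

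Table 3 puts the highest scheduled step, 72 g/day, on Days 5 to 14, and section 4.1 ends intake on Day 14. Under section 8.4.3, Baseline is averaged over Days -2, -1 and 1 before the first dose, and EOI over Days 12, 13 and 14. Controls receive supportive self care alone, with no placebo, and the trial is open label (sections 6.4 and 6.10).

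Section 8.4.3 gives Kaplan-Meier estimates by arm for time to resolution. For change to EOI it gives an ANCOVA group difference with a 95% CI. It applies both methods to both composites.

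**The concern.** Two of the 13 items can be raised by the illness or by the product, and only one arm takes the product. Baseline is free of product effect in both arms, while the EOI window lies wholly inside the highest scheduled dose step. The protocol has no rule for attributing a GI score to COVID-19 or to KB109 within the composite. Section 7.3.3 deals only with which symptoms are recorded as adverse events.

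The between-arm contrast on the 13-item score therefore mixes the course of the illness with tolerability of the product. If KB109 looked slower or less improved on this score, the score alone could not say which of the two was responsible. The protocol names neither composite as the basis for the comparison and does not say how a disagreement between them would be read.

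**Working it through.** **The scale.** 13 items x 3 = 39, which reproduces the stated range of 0 to 39. The two GI items can add 2 x 3 = 6 points, or 6/39 = 15%.

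**What blocks resolution.** The sum must be 0 or 1. Take a patient with every other symptom absent:

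| GI disturbance | Diarrhea | Sum | Meets the rule that day |
|---|---|---|---|
| 1 | 0 | 1 | yes |
| 1 | 1 | 2 | no |
| 2 | 0 | 2 | no |
| 0 | 2 | 2 | no |

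Because the rule is a sustained one, a GI sum of 2 late in the Intake Period postpones resolution until that score clears. A GI effect that ends on Day 9 leaves resolution on Day 10 possible. Section 4.1 collects symptoms weekly after Day 14, so a patient blocked through Day 14 might not be recorded as clear until about Day 21.

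**Size for time to resolution.** The protocol gives no median and no rate of GI scores by arm. Assumptions:
- no true effect of KB109 on the illness;
- exponential resolution times with a 12-day median in both arms;
- an excess share q of KB109 patients held at a GI sum of 2 or more through Day 14.

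SSC resolved by Day 14: 1 - 2^(-14/12) = 55.5%. KB109 resolved by Day 14: (1 - q) x 55.5%.

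The 95% half-width of the difference is 1.96 x sqrt[p1(1-p1)/170 + p2(1-p2)/170]. The 170 per arm is the protocol's upper evaluable number (400 x 0.85 / 2).

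| q | KB109 by Day 14 | Difference | Half-width |
|---|---|---|---|
| 10% | 49.9% | about -5.5 points | 10.6 points |
| 20% | 44.4% | about -11 points | 10.6 points |
| 40% | 33.3% | about -22 points | 10.3 points |

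Varying the median:
- 10 days: SSC 62.1%; differences -6.2, -12.4 and -24.8 points.
- 15 days: SSC 47.6%; differences -4.8, -9.5 and -19.1 points.

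The reported median moves too. With a 10-day median in SSC, solving (1 - q)(1 - 2^(-t/10)) = 0.5 gives t = 11.7 at q = 10% and 14.2 at q = 20%, that is, Day 12 and Day 15 when counted in whole days. At q = 20% a patient still blocked on Day 14 resolves on Day 15 at the earliest.

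**Size for change to EOI.** The shift in the group difference is q x s, where s is the mean number of GI points added in affected patients (also an assumption):
- q = 10%, s = 1: 0.1 points
- q = 20%, s = 2: 0.4 points
- q = 40%, s = 4: 1.6 points

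**Without the two items.** An 11-item score runs from 0 to 33 (11 x 3), and the direct contribution of the GI items is zero by construction. The same is true of the 8-item score (0 to 24).

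**The case against.** The protocol already has a partial safeguard. Both 13-symptom endpoints have an 8-cardinal counterpart without GI items, with the same resolution rule, methods and subgroups. Section 3.2.3 also plans change to EOI for each symptom, which would show GI symptoms that emerge on product. A divergence between the two composites could therefore be traced, and a reader who infers that a null or unfavourable result would be uninterpretable goes too far. What remains is that the 8-item score also drops fatigue, nasal congestion and chest tightness, that the item-level proportions in section 3.2.2 cover only patients with the symptom at Baseline, and that no composite is named for the comparison.

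The secondary objective is to evaluate measures of health, and GI symptoms are collected as COVID-19 symptoms. Total symptom burden is thus a legitimate quantity. This stands, and is a reason to keep the 13-item score.

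Three stronger readings are tempting, and the document supports none of them:
- *Any product GI effect prevents resolution until dosing stops.* One mild GI item alone scores 1 and meets the rule, and effects that end earlier leave later days open.
- *Table 4 supplies q.* Its 10% to 60% rates are precision inputs for any SP-related TEAE, of any type or duration. They are not rates of a GI score of 2 or more lasting to Day 14. Down-titration or interruption (section 6.8), permitted antidiarrheals (section 6.6) and rapid reversibility (section 2.3) all work against persistence. The diarrhea statement in section 7.3.1 refers to still higher amounts, with no threshold given.
- *The endpoint as a whole is biased against KB109.* Only the contribution of these two items has a known direction. Open-label self-report could favour KB109.

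Finally, the trial is descriptive. Time to resolution has no planned between-arm test or difference, and only the ANCOVA gives a group contrast. That limits formal consequences but does not remove bias from the estimates.

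**Conclusion.** The point holds as a predictable, one-directional contribution of two items to two secondary endpoints. It follows from the composite's content, the listed product effects, the timing of Baseline and EOI relative to dosing, and a control arm without product.

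Its size is conditional on assumed inputs. For resolution by Day 14 it runs from about half the 95% half-width (q = 10%) through roughly equal to it (q = 20%) to about twice it (q = 40%). For change to EOI it is modest. The primary safety endpoint and the sample-size precision table are unaffected. It is an improvement worth making because it is nearly free.

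**What to change.** In sections 3.2.2 and 8.4.3:
- Add an 11-symptom composite (the 13 less GI disturbance and diarrhea) for time to resolution and for change to EOI, with the methods already specified.
- State, before results are seen, that the KB109 versus SSC reading rests on the 11-symptom and 8-cardinal composites.
- Keep the 13-item score, described as total symptom burden from any cause.
- Summarise the two GI items by arm for all patients, not only those with the symptom at Baseline.

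The cost is one derived score from data already collected, with no change to any procedure. The small downside is that COVID-19 GI symptoms are then reported apart from the composite used for the comparison.

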### 3.2.3 Exploratory Endpoints

The exploratory endpoints are as follows:

- Change from Baseline to EOI in individual COVID-19 related symptom score: cough, chills/repeated shaking with chills, muscle pain, fever, headache, anosmia/ageusia, shortness of breath, sore throat, gastrointestinal disturbance/symptoms, diarrhea, fatigue, nasal congestion, and chest tightness
- Individual measures of quality of life (QOL)
- Change from Baseline to EOI in bedrest time measured as patient-assessed daily cumulative total rest (measured in hours)
- Proportion of patients with increases in patient global impression on COVID-19 condition (PGIC)
- Proportion of patients with temperature below 100.4 °F without an anti-pyretic medication
- Change from Baseline (Day 1) in:
  - Laboratory measures
  - Biomarkers of infection, antibody response, and inflammation (e.g., D-dimer, lipocalin, cytokines, IgM/IgG sero-conversion, and Neutralization Assays)

## 4 STUDY DESIGN

### 4.1 Overall Design

This study is a randomized, controlled, multi-site, open label clinical study. It is intended to assess KB109 on safety as well as measures of signs, symptoms, healthcare utilization (including hospitalizations), laboratory/biochemical indices and QOL measures in outpatients who have tested positive with COVID-19, have mild-to-moderate disease, and have been advised to manage their disease at home with SSC under quarantine protocols set forth by the CDC ([CDC 2020](#)) or local ordinances or practices as advised by their healthcare provider.

Approximately 350–400 patients will be randomized (1:1) to receive either SSC + KB109 or remain on SSC alone. The randomization will be stratified by site/center, age subgroup ( $\geq 18$  to  $<45$  years,  $\geq 45$  to  $<65$  years,  $\geq 65$  years), and comorbidity status (Yes, No); see [Section 8.1](#) for

further details. The study consists of a Screening/Randomization Visit, Intake Period (14 Days) followed by a 21-day Follow-up Period (Figure 4).

Details of the procedures and assessments conducted during the study are provided in Section 4.3, and the timing for each is presented in the Schedule of Assessments (SOA; Table 1) and summarized in Figure 4.

To be eligible for the study, patients must be at least 18 years of age, have tested positive for COVID-19, and be medically stable at study entry per eligibility criteria. Patients must have also been advised by a healthcare provider that self-management of COVID-19 is indicated; eligibility criteria are detailed in Section 5.1 and Section 5.2.

Patients will be recruited via outpatient clinics or testing centers performing SARS-CoV-2 testing or via online portals. They will have an opportunity to voluntarily consent into the study either at the time they are making their outpatient clinic appointment, at the outpatient testing center/clinic itself, or following discharge from the outpatient clinic. SARS-CoV-2 tests (RT-PCR test, antigen test or equivalent test to detect active infection) are part of the standard of care, though may be provided as part of the study procedures at some sites. Results from a local testing clinic that is not the study site location may be used to determine eligibility virtually (not at site). Patients who are symptomatic at the time of getting a positive COVID-19 test result and meet eligibility criteria will enter Part 2 of the study within 48 hours of testing positive. Patients who are pre-symptomatic at the time of testing, develop symptoms within 7 days of testing positive and meet eligibility criteria will enter Part 2 of the study within 5 days of the symptoms showing. All enrolled patients will have same level of care and same procedures conducted.

## Part 1

This study comprises two parts. In Part 1, patients who consent to the study will undergo a full assessment of inclusion and exclusion criteria (Section 5.1 and Section 5.2). If feasible blood samples for Baseline hematology, chemistry, biomarkers and serological markers of immunity, and nasal and oropharyngeal swabs for quantitative viral load assessments (research purposes only) will be taken (See Section 4.3.9 and Table 1); sample collection may occur at the patient's home by a healthcare professional, remotely, or at the study site or clinic. Patients will be asked to begin recording COVID-19-related symptoms using a secure website called "TrialPace™ diary" (TrialPace™) with a unique log-in and password.

It is possible that patients may only consent to Part 1 of this study initially. If a positive test result for COVID-19 is received, then the patient may be contacted by the study team (or designee such as a centralized telemedicine provider, physician or nurse practitioner) to review study eligibility criteria and obtain informed consent.

Information entered into TrialPace™ for patients who are deemed ineligible for the study will not be used for any purpose.

## **Part 2**

Only patients who have a positive test result for COVID-19 can continue to Part 2 of this study. Part 2 of the study comprises an Intake Period and a Follow-up Period. In Part 2, following confirmation of eligibility criteria, the site will notify an independent, third party vendor that a patient is eligible for randomization no later than 48 hours after a positive test result is received by the patient for COVID-19. Upon randomization (SSC + KB109 or SSC alone), a Kaleido at-home Study Kit (KaSK) and SP (KB109) and dosing instructions (as applicable) will be shipped via overnight delivery to the patient's home. The KaSK will include a thermometer, a pulse oximeter, and telemedicine contact information. Patients should continue to record COVID-19-related symptoms using TrialPace™ until the KaSK is delivered.

### **Part 2, Intake Period**

The Intake Period (Days 1-14) will begin the morning after receipt of the KaSK. All patients will continue to follow the SSC guidance as provided by the treating healthcare provider throughout study participation. In the Intake Period, all patients will continue to record their daily COVID-19-related symptoms, selected COVID-19 signs, responses to questions related to QOL measures, healthcare utilization measures, and concomitant medications taken in the previous 24 hours using TrialPace™ where appropriate. Patients randomized to SSC + KB109 will begin consuming KB109 on Day 1 after recording the required information. All KB109 usage will be noted in the patient's SP log. For all patients in both groups, temperature and oxygen saturation will be measured and recorded as needed throughout the day prior to taking anti-pyretic medication.

Wellness visits by telephone call between Day 1 and Day 14 will be conducted to follow-up on the patient's health status, to ascertain compliance with SP usage or completion of TrialPace™ questions, and to reeducate the patient on the importance of adherence to study instructions including SP usage (where applicable). When wellness and telemedicine visits fall on the same day, they will be combined as a telemedicine visit.

On Day 14, all patients will undergo a telemedicine visit where the following will be conducted: an abbreviated physical examination, an assessment of safety and other protocol-specified measures of health, and an evaluation of whether follow-up treatment is recommended due to a deterioration of COVID-19 symptoms. Patients in the SSC + KB109 group will stop taking KB109 on Day 14. If feasible blood samples for clinical chemistries, biomarkers and serological measures of immunity, and nasal/oropharyngeal swabs for quantitative viral load assessments (research purposes only), will be collected; sample collection may occur at the patient's home by a healthcare professional, remotely, or at the study site or clinic.

## Part 2, Follow-up Period

On Day 15, all patients will enter the Follow-up Period (Days 15 to 35) where COVID-19 signs, symptoms and healthcare utilization indices will be collected weekly in TrialPace™ where appropriate. On Day 14, the Investigator will instruct the patients to stop the intake and return the SP during the Follow-up Period (Days 15 to 35). In addition, wellness visits by telephone call will be conducted on Days 21, 28, and 35 to follow-up on the patient's health status.

On Day 35, all patients will undergo another telemedicine visit where the following will be conducted: an abbreviated physical examination, an assessment of safety and other protocol-specified measures of health, and an evaluation of whether follow-up treatment is recommended. When wellness and telemedicine visits fall on the same day, they will be combined as a telemedicine visit. If feasible blood samples for clinical chemistries, biomarkers and serological measures of immunity, and nasal/oropharyngeal swabs for quantitative viral load assessments (research purposes only) will be collected; sample collection may occur at the patient's home by a healthcare professional, remotely, or at the study site or clinic.

For convenience, standard terms language included in International Conference for Harmonization (ICH) guidance relevant to the conduct of clinical trials are used in this protocol. An example of such a term used in this protocol is "treatment emergent," included in ICH E9. Use of this standard term is not intended to connote treatment with a medicinal product administered (ICH E9 2018).

Throughout the study, safety will be monitored by TEAEs, clinical signs and symptoms, and selected vital signs (i.e., temperature and oxygen saturation). Concomitant medications/supplements will be recorded throughout the study. Any patient experiencing a TEAE, or intolerable GI symptoms will be evaluated by the principal investigator (PI) or telemedicine provider for possible interruption and/or down-titration of SP dose to the previously tolerated level in consultation with the medical monitor.

In the event of significant worsening of COVID-related symptoms or two sequential pulse oximetry readings of <94% within 2 minutes, patients will be instructed to seek medical attention immediately (see [Section 6.7](#)).

In the event of worsening GI symptoms of other attributable AEs, the SP may be down titrated or temporarily interrupted (see [Section 6.8](#)). Details of the patient's SP dose (including the date, time, and amount) will be recorded in SP dosing logs.

See [Section 4.3](#) for further information on the study procedures, and [Table 1](#) for the SOA.

**Figure 4 Study Design**

[figure not shown]

*Abbreviations: BID = Twice daily dosing; SSC = Supportive self-care*

An interim analysis is planned when approximately 40% of the total randomized patients have completed or discontinued prior to completion of the EOI period (See [Section 8.4.6](#)).

